#### Implementation

In order to implement the GESCO intervention in the care of patients with CNCP, the following implementation strategies [49] will be applied:

Educational training for GPs: Based on current knowledge GPs will take part in two educational sessions addressingPharmacotherapy (targeted use of assessments, i.e., in order to screen for opioid use disorder; sex-specific pharmacotherapy; drug therapy safety)Strategies for patient empowerment (concepts for “de-chronification” in CNCP in consideration of the pain medications’ role for patients and their significance for coping with everyday life)Communication training (narrative interview techniques to facilitate a sex-, gender-, and diversity-sensitive exploration of patients; health-oriented conversation in order to promote patients’ health competencies and salutogenesis)Self-reflection (reflection of the GPs’ own medical actions in consideration of sex- and gender-sensitive aspects; reflection of the GPs’ individual gender role and gender awareness; introduction of mind–body approaches, i.e., stress management approaches, including practical exercises on how to instruct patients).Case conferences: online quality circles for GPs to discuss care management of patients with CNCP.Support: Materials and infrastructure facilitating the sustainability of the intervention in daily routine, i.e., handouts regarding communication strategies and a pharmacological hotline.

The training program will be developed in accordance with the principles for resilient learning programs of Haraldseid-Driftland and colleagues [50].

#### Intervention

The GESCO intervention comprises a sex- and gender-sensitive care concept for patients with CNCP in primary care. Applying knowledge and skills from the previous educational training, GPs will conduct two counseling sessions within 6 to 8 weeks with each of the study patients. During the counseling sessions, they are requested to obtain an expanded medical history also considering sex and gender aspects, perform a medication analysis, provide resource-oriented counseling, and—if necessary—refer the patients for psychosocial support.

The final choice of which intervention content to apply will be left to the GP’s discretion depending on the patient’s needs.

#### Outcomes

With the overall goal of determining whether a larger effectiveness trial is appropriate, this study will simultaneously test (a) the feasibility of implementing the intervention and of the trial methods and (b) the intervention’s clinical outcomes [38]:Implementation measures will be assessed to obtain detailed information on the implementation process and its feasibility (Table 1).Patient-centered clinical outcomes will be assessed to evaluate the instruments’ appropriateness and to determine preliminary effects, which will—also considering clinical relevance and results from other studies—provide the basis for an effect size estimation for a future larger effectiveness trial (Table 2).

**Table 1 Tab1:** Feasibility measures based on Pearson et al. [38]

*Measure*	*Criteria*	*Data collection*	*Date of data collection*

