**Methods:**

The development process is designed in accordance with the first two phases of the UK Medical Research Council. Phase I will iteratively explore, develop, and pilot the intervention’s modules using literature searches, interviews, and workshops involving stakeholders and experts. Phase II will pilot-test the novel intervention in a sample of 40 patients with CNCP under LTOT from ten general practices using an effectiveness-implementation hybrid design including a mixed-methods process evaluation focusing on implementation strategy criteria and a single-arm, pre-post comparison to determine preliminary effects in preparation for a larger effectiveness trial. The intervention will combine in-person educational sessions for general practitioners and tools to be used in patient care.

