### Objectives

The aims of the study are twofold: The first is to develop a novel gender-sensitive care for chronic non-cancer pain patients receiving long-term opioid therapy (GESCO) intervention to support individuals with CNCP receiving LTOT in primary care. In this step, the elements of the GESCO intervention including implementation strategies required to apply the intervention in the care of patients with CNCP will be developed. The second is to determine the feasibility of this intervention from the perspective of patients with CNCP and their general practitioners (GPs). This feasibility study aims to identify potential refinements to the intervention’s contents and design prior to a larger effectiveness trial, and to determine preliminary effects to estimate effect sizes for a larger trial [37, 38].

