#### Sample size and recruitment

Ten GPs from different general practices will be recruited for the feasibility study, excluding those practices and GPs that already participated in the development process. Again, GPs will be informed about the study and invited to participate during training sessions at the university and via email distributed to the institutes’ teaching and research practice network. Considering a patient drop-out rate of 20% and a target sample size of 40 patients for the analysis, each of the ten GPs will recruit five patients fulfilling the eligibility criteria defined for the study. This sample size is sufficient to detect, e.g., a mean difference (before and after intervention) of 0.5 on the 10-point-pain scale with a standard deviation of 1 (alpha = 0.05, power = 80%, 2-sided one-sample-*t*-test).

In order to ensure that the patients recruited for the feasibility study will match the eligibility criteria, study team will provide the GPs comprehensive written information and guidelines on how to conduct the feasibility study. To assess fidelity to the protocol, the study team will conduct study monitoring by periodic checks and also provide ongoing support to the GPs, ensuring they understand and adhere to the established procedures. This monitoring will help maintain consistency and compliance throughout the study.

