## Discussion

The GESCO study will examine how the diversity of the experience and processing of pain in patients on LTOT of differing sex and gender can be addressed appropriately and in a quality-enhancing manner in the therapeutic setting. As a result, it will provide a novel personalized concept for the care of patients with CNCP, integrated into preliminary analyses and a subsequent feasibility assessment to ascertain the suitability and implementability of the intervention. It will also be used to pilot the study instruments and measures. Our results regarding the implementation measures will be evaluated to determine the suitability of the intervention for transfer to an efficacy trial. If necessary, the intervention will be adapted or (in the worst case) rejected. The progression criteria, as outlined by Thabane and Lancaster [41] and suggested by Pearson et al. [38], will be used to guide this assessment. The limited sample size of the GESCO study restricts the generalizability of possible interventional effects but the results of this study build a foundation to estimate the sample size for a subsequent cluster randomized controlled trial taking into account the standard deviation. Additionally our estimation will be complemented by other studies from the literature applying the same outcome measures.

By considering sex and gender differences in health care and proposing a sex- and gender-sensitive care concept, the GESCO study team is doing pioneering work, which might also be transferable to other health care scenarios and thereby help improve disease management.

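### The single-arm pre-post change cannot serve as the between-arm effect of the later cluster randomised trial; if it does, that trial is undersized whenever control patients also improve

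*Protocol article*

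**What the plan says.** The abstract describes the quantitative part of Phase II as "a single-arm, pre-post comparison to determine preliminary effects in preparation for a larger effectiveness trial". The Phase II data analysis section compares baseline with follow-up by paired tests.

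Three places say what the result is for:

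- **Objectives:** the feasibility study is "to determine preliminary effects to estimate effect sizes for a larger trial". No qualifier is attached.
- **Phase II, Outcomes:** the preliminary effects are to "provide the basis for an effect size estimation for a future larger effectiveness trial". The same sentence adds "also considering clinical relevance and results from other studies".
- **Discussion:** the results "build a foundation to estimate the sample size for a subsequent cluster randomized controlled trial taking into account the standard deviation". The next sentence says that "our estimation will be complemented by other studies from the literature applying the same outcome measures".

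The pre-post change is therefore not the only planned input, but it is the one called the basis. None of these places says that a within-patient change differs from a between-arm difference, or allows for change that would occur without the intervention. The Discussion's caveat is that the small sample restricts generalisability, which is a different matter.

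**The concern.** The later trial will estimate intervention minus control. The pilot estimates follow-up minus baseline in treated patients only. The two agree only if untreated patients would not change on average.

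Several things can move the pilot figure without any intervention effect: the natural course of chronic pain, regression to the mean, repeated study contact by telephone, and selection of patients by their own GPs. Eligibility sets no minimum pain score, so regression to the mean would come through whom the GPs choose and when, not through an entry threshold. One arm cannot separate these from the effect of the intervention.

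There is also a scale problem. A paired effect size divides the change by the SD of the change. A between-arm standardised difference is commonly expressed in SDs of the outcome. The two differ by a factor that depends on the correlation between t0 and t2.

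Preparing the next trial is one of the stated purposes of the quantitative part. If the pre-post figure becomes the target difference, the later trial may be too small to detect the effect that exists.

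**Working it through.** **1. The plan's own figure.** Phase II, Sample size and recruitment, gives a "mean difference (before and after intervention) of 0.5 on the 10-point-pain scale with a standard deviation of 1", two-sided alpha 0.05, power 80%, one-sample t-test, 40 analysed, 20% drop-out. By the noncentral t distribution, 34 patients give 80.8% power and 40 give 86.9%. Drop-out: 40 / (1 − 0.20) = 50. The statement that 40 is sufficient is correct and conservative. It has no bearing on this point.

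**2. Precision of the pilot change.** With n = 40 and SD 1, the 95% CI half-width is t(0.975; 39) × 1/√40 = 2.023 × 0.158 = 0.32. An observed 0.5 has a CI of 0.18 to 0.82, ignoring clustering.

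**3. The pilot change used as the between-arm effect.** Assumptions, because the protocol gives no figures: the treated arm improves by 0.5, SD 1 in both arms for the quantity compared, two-sided alpha 0.05, 80% power, before clustering.

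n per arm ≈ 2(1.960 + 0.842)² × SD²/δ². For δ = 0.5 this is 2 × 7.85/0.25 = 62.8, so 63 by the normal approximation and 64 by the t-test.

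If control patients change by c, the true difference is δ = 0.5 − c:

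| Control-arm improvement c | True δ | Needed per arm (t-test) | Power at 64 per arm |
|---|---|---|---|
| −0.2 (worsening) | 0.7 | 34 | 98% |
| −0.1 (worsening) | 0.6 | 45 | 92% |
| 0 | 0.5 | 64 | 80% |
| 0.1 | 0.4 | 100 | 61% |
| 0.2 | 0.3 | 176 | 39% |
| 0.25 | 0.25 | 253 | 29% |

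**4. The scale.** With equal SDs at t0 and t2 and correlation r, SD of change = SD × √(2(1 − r)). A change of 0.5 change-SDs then equals 0.5 × √(2(1 − r)) outcome-SDs. For assumed r = 0.3, 0.5 and 0.7 this is 0.59, 0.50 and 0.39. The paired value transfers unaltered only at r = 0.5, or if the later trial is analysed on change scores with the same SD.

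**5. What the pilot can supply.**

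- SD at n = 40: the 95% limits are √(39/χ²) with 39 df, or 0.82 to 1.28 times the estimate. This is usable if the uncertainty is carried forward.
- ICC from 10 practices with 4 patients each: F = (1 + 3 × 0.05)/(1 − 0.05) = 1.21 for an assumed estimate of 0.05. With 9 and 30 df, the 95% CI for the ICC is about −0.15 to 0.45. This is too wide to plan on alone.

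**The case against.** The strongest reply is that the protocol already names the other inputs. The Outcomes sentence adds clinical relevance and other studies, and the Discussion adds literature with the same outcome measures. A reader might infer that the pre-post change alone fixes the effect size, or that the SD is the only sizing input. The text supports neither reading. What stands is narrower: the pre-post change is still called the basis, the Objectives carry no qualifier, and neither clause requires the other studies to be controlled. Literature on the same instruments could be more pre-post data.

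A reader might also infer that the later trial will be undersized. The documents do not support that either. They give no control-arm change. With none, 64 per arm is right, and with worsening it is too many. Improvement without the intervention is plausible but assumed.

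Nor should every non-specific component be counted as bias. The two counselling sessions are the intervention. Against usual care, the effect of their attention belongs to the between-arm difference, and the later trial's control condition is not specified.

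It is also fair to say that drop-outs are already recorded (Table 1), that t0 and t2 data are already collected (Table 2), and that an article need not list every planning parameter of a later trial. The absence of an ICC or correlation is therefore not an error. Finally, sizing is not the only purpose of the quantitative part: it also tests whether the instruments are appropriate.

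**Conclusion.** The point holds as a stated use that the design cannot support. A single-arm change does not estimate a between-arm difference, and the three places that link it to the later trial's effect size or sample size do not correct for this. The other named inputs soften the problem without removing it.

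The consequence is conditional. If 0.5 were carried over, improvement of 0.1 to 0.25 in control patients would cut power from 80% to between 61% and 29% before clustering. These figures rest on the assumed SD of 1, on 0.5 being used on the same scale in both designs, and on control-arm changes for which the protocol gives no value.

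The conduct, safety and analysis of this pilot are unaffected. What changes is what its quantitative result may be used for, and that should be corrected.

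**What to change.** Reword the Objectives, the Phase II Outcomes section and the Discussion along these lines:

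- The target difference for the later trial is set from clinical relevance and controlled external evidence.
- The pre-post change is reported descriptively with its confidence interval and is not used as the effect size.
- The pilot supplies the outcome SD with its uncertainty, the t0-t2 correlation, retention and recruitment.
- The ICC comes mainly from external sources. The pilot's own ICC, if reported, is given with its confidence interval.

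How cautiously to treat the SD, for example by using an upper confidence limit instead of the point estimate, is a matter of judgement for the later trial.

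The cost is wording only: no new patients, data or procedures. The downside is that the later trial may turn out to need a larger sample than the pre-post figure would have suggested.

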**Implementation measures addressing the recruitment process**			
Reach	Recruitment of 10 practices for the study successful within 3 months	Documentation sheet, completed by study center	Continuously during practice recruitment and study conduct
	Success of different recruitment strategies applied for GP recruitment		
	Drop outs (GPs and patients)		
	Recruitment of 50 study patients by 10 practices successful within 3 months	Documentation sheet, completed by the practices	Continuously during patient recruitment
	Patients willingness to receive the GESCO intervention/participate in the study	Qualitative interview with GPs	After completing two consultations per study patient (t1)
**Implementation measures addressing the educational training for GPs**			
Adoption	Uptake (participation in educational trainings)	Documentation sheet, completed by study center	After educational training
Acceptability	If GPs find the intervention’s components agreeable	Evaluation sheet, completed by GPs	After educational training
Self-efficacy	Self-perceived capacity to undertake implementation		
**Implementation measures addressing the intervention on patient level**			
Fidelity	Degree to which interventional components are implemented as intended by designers (adherence)	Documentation sheet for each consultation with study patient, completed by GP	After each patient contact
Feasibility	Perceived fit of the intervention for everyday use	Qualitative interview with GPs	After completing two consultations per study patient (t1)
Adaptability	Adaptability of the intervention’s components to meet local needs		
Satisfaction	Satisfaction with the implementation strategies and intervention		
**Sustainability of implementation**			
Sustainability	Uptake of intervention	Qualitative interview with GPs incl. the G-NoMAD [53]	After completing two consultations per study patient (t1)
		Written questionnaire incl. the G-NoMAD [53], completed by GP	Simultaneously with last patient-out per practice

**Table 2 Tab2:** Patient-centered clinical outcomes

*Outcome*	*Measure*	*Data collection*	*Date of data collection*		
			*t0*	*t1*	*t2*
Pain	Pain history and progression (German Pain Questionnaire [58])	Self-assessment, completed by patient	x		x
	10-point-pain scale (three scales: acute pain, average pain during the last 4 weeks, and strongest pain within the last 4 weeks)	Telephone interview with patient, conducted by study nurse	x	x	x
Mental well-being	Depression-Anxiety-Stress Scale (DASS) [59]	Self-assessment, completed by patient	x		x
	The Marburg questionnaire on habitual well-being (FW7) [60]				
Quality of life	Veterans RAND 12-Item Health Survey (VR-12) [61]				
Pain medication	Self-reported medication	Telephone interview with patient, conducted by study nurse	x	x	x
	German, nationally standardized medication plan	Assessed by treating physician	x	x	x
Adverse effects of medication	Self-reported adverse effects	Telephone interview with patient, conducted by study nurse	x		x
Satisfaction with information about medication	Satisfaction with Information about Medicines Scale (SIMS) [62, 63]				
Potential opioid medication misuse	Pain Medication Questionnaire (PMQ) [64]				
Perceived stigma due to pain	Internalized Stigma of Chronic Pain (ISCP) [65]^a^				
Disruption of daily life due to pain	Pain Disability Index (PDI) [66]				
Optimism/pessimism	Optimism–Pessimism Short Scale 2 (SOP2) [67]				

*t0* baseline (before intervention); *t1 *2-month follow-up; *t2 *5-month follow-up

^a^German translation by study team

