#### Data collection and data management

Data from the participating GPs will be collected immediately after recruitment, after participation in the training, during implementation of the GESCO intervention in patient care, and after completing the intervention for all study patients (Table 1).

After recruitment, GPs will complete a written questionnaire on practice characteristics, sociodemographic characteristics, and gender awareness (Nijmegen Gender Awareness in Medicine Scale N-GAMS [50, 51]).

After participation in the educational sessions, GPs will provide written feedback regarding the sessions’ content, the materials used, the acceptability of the intervention within their practice, and their self-efficacy to apply the intervention in patient care. Also, the practices’ Organizational Readiness for Implementing Change will be assessed using the validated ORIC questionnaire [51, 52].

When implementing the intervention in CNCP care, GPs will complete a documentation sheet for each patient consultation which assesses the duration, main contents and results of the consultation, the interventional elements applied, and the GPs personal impression of the consultation. These quantitative data will be manually entered into an electronic data capture system.

For data collections with GPs that will be conducted after completing the intervention for all study patients, qualitative and quantitative methods will be applied. Immediately after finishing two consultations per study patient, a semi-structured telephone interview will be conducted with each GP (Supplementary Material 3). These interviews will be audio-recorded and transcribed afterwards. During transcription, data will be pseudonymized using a unique identification number per GP in order to link the interview data to the quantitative data assessed per physician. Accompanying the interview, the Normalization Process Theory Measure (G-NoMAD) [53, 54] will be obtained to assess the implementation process. Simultaneously with the last patient-out per practice, each GP will complete a questionnaire on sustainability aspects, which will again include the G-NoMAD [53].

In addition to the feasibility aspects assessed from the GPs, aspects on the methods’ feasibility related to the recruitment process and the implementation will be documented by the study team in order to prepare a future larger effectiveness trial (Table 1).

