For patients, data will be collected three times: after enrollment (baseline, t0), about 2 months later (immediately after completing the intervention, t1), and 5 months after baseline (t2) (Table 2). All data for the patient-centered pre-post comparison, including self-reported prescribed and over-the-counter medication, will be collected from the patients via phone at baseline and after 5 months. To describe the study population sociodemographic data, gender-related variables for health research (GVHR [55], German translation by study group), and experience of social support (Oslo Social Support Scale OSSS-3 [56, 57]) will be collected at baseline. This procedure will be facilitated by a study nurse who will enter the data directly into an electronic data capture system. The data collection at 2 months will consist of a qualitative, semi-structured telephone interview and will focus on feasibility outcomes (Supplementary Material 4). In detail, the open-ended questions will address the patients’ experience with the intervention and their study participation. This includes their satisfaction with the intervention, their acceptability of the intervention, especially regarding the gender approach, and how they perceived the communication with their GP, with the study center and the data collection process. In addition to qualitative, open-ended questions, any changes in medication use since baseline will be assessed. The interview part on patients’ experiences will be audio-recorded and transcribed verbatim, whereas the data on medications will be entered directly into the electronic data capture system. Qualitative interview data will be pseudonymized using a unique identification number per patient in order to link the interview data to the quantitative data assessed for the pre-post comparison. Additionally, GPs will complete a documentation sheet for each participating patient at baseline and after 5 months, providing information on chronic diseases and prescribed medication. Medication use will be analyzed after Anatomical Therapeutic Chemical coding and in consideration of drug dosages and frequency of administration.

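### Self-reported adverse effects of medication are not scheduled at t1, when the intervention ends; adding the existing item to the existing t1 call is a cheap improvement

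*Protocol article*

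**What the plan says.** Table 2 of the protocol article (Patient-centered clinical outcomes) lists "Self-reported adverse effects", collected by a study nurse by telephone, with marks at t0 and t2 and none at t1. The Phase II section on data collection and data management agrees: the data for the pre-post comparison "will be collected from the patients via phone at baseline and after 5 months".

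The same section places the follow-ups "about 2 months later (immediately after completing the intervention, t1), and 5 months after baseline (t2"). The Intervention section states that "GPs will conduct two counseling sessions within 6 to 8 weeks with each of the study patients", and that in these sessions the GPs are asked, among other things, to "perform a medication analysis".

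The t1 contact "will consist of a qualitative, semi-structured telephone interview and will focus on feasibility outcomes". It also has a medication component: "any changes in medication use since baseline will be assessed". Table 2 marks the three pain scales and self-reported medication at t1, both by nurse telephone interview, which is the mode used for the adverse-effect item.

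**The concern.** The medication review takes place before t1, and the t1 contact asks whether medication has changed. The study will therefore know at t1 that a patient's medication was altered, and will have pain scores for that time, but will have no matching structured answer on adverse effects. Pain and tolerability are followed on different schedules over the period in which the intervention is delivered.

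Two consequences follow. Effects that appear during the intervention and settle before month 5 reach the dataset only if the patient recalls them at t2 or they surface somewhere unstructured. And a patient who leaves before t2 has no scheduled adverse-effect report after baseline. The study is also meant to try out instruments and measures for a later cluster randomized trial, so a schedule that is not tested at t1 may be carried forward.

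**Working it through.** **Inputs from the protocol article**
- Recruited: 10 GPs × 5 patients = 50 (Sample size and recruitment, Phase II).
- Planned drop-out 20%; target for analysis 40 (same section).
- t1 at about 2 months, t2 at 5 months (Data collection and data management; Table 2 footnote).
- Two sessions within 6 to 8 weeks (Intervention).
- Adverse-effect item: t0 yes, t1 no, t2 yes (Table 2).

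**Step 1: the plan's own figure.** 40 / (1 − 0.20) = 50, which equals 10 × 5, so the recruitment figure reproduces. The power statement also holds: for a difference of 0.5, SD 1 and two-sided alpha 0.05, the one-sample t-test needs n = 34 (power 80.8%; n = 33 gives 79.5%), and n = 40 gives 86.9%. Neither figure depends on the assessment schedule.

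**Step 2: the t1 schedule.**

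| Item | t0 | t1 | t2 |
|---|---|---|---|
| Pain scales (nurse telephone interview) | yes | yes | yes |
| Self-reported medication (nurse telephone interview) | yes | yes | yes |
| Self-reported adverse effects (nurse telephone interview) | yes | no | yes |

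The pain scales at t1 rest on Table 2 alone. The text on the t1 contact names the qualitative questions and medication changes.

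**Step 3: the gap.** 5 months − about 2 months = about 3 months between the end of the intervention and the first scheduled post-baseline adverse-effect question.

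**Step 4: patients without a scheduled post-baseline report.** 50 × 0.20 = 10, taking every drop-out as missing the t2 call. Coverage is then 40 of 50.

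**Step 5: what a t1 question would add among drop-outs.** Let f be the share of the 10 drop-outs who leave after t1. Patients with at least one post-baseline report = 40 + 10f. The article does not give f, so the whole range is shown:

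| f (assumed) | t2 only | t1 and t2 |
|---|---|---|
| 0 | 40 of 50 | 40 of 50 |
| 0.5 | 40 of 50 | 45 of 50 |
| 1 | 40 of 50 | 50 of 50 |

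Patients who leave before t1 are missed either way. For everyone reached at t1, the item also adds a report at the end of the intervention.

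**Step 6: other listed sources.** The GP sheet for each consultation covers duration, "main contents and results of the consultation, the interventional elements applied, and the GPs personal impression of the consultation". The open t1 questions cover experience with the intervention and with study participation. Neither description names adverse effects.

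**The case against.** The schedule is internally consistent. Table 2 and the text agree, several other instruments in Table 2 follow the same t0/t2 pattern, and the t1 contact is built as a feasibility interview. The article does not offer this row as the trial's safety monitoring. The intervention requires a medication analysis, not a change, and leaves the choice of content to the GP, so the number and timing of changes are unknown. Some changes may come after t1, where only t2 can pick them up. In a single-arm pilot with 40 patients analysed, t1 adverse effects could not be attributed to the intervention. All of this stands. It makes the point an improvement to a coherent schedule and not the correction of an error.

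A reader might go further and infer that early effects are lost, or that drop-outs yield no safety data at all. The article does not support either reading. The recall period of the t2 question is not stated, so earlier effects may be reported then. The t1 interview guide is supplementary material that is not shown, and any separate adverse-event procedure would normally sit in the full protocol. The open t1 questions or the GP's note of consultation results may also pick some effects up. Nor can the size of any under-count be given. That would need assumed rates of onset and resolution, and effects arising by month 2 are a different quantity from effects present at month 5.

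What the objection does not remove is that no listed source provides a structured t1 answer comparable with t0 and t2, although the t1 contact already asks about medication.

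**Conclusion.** The point holds as a cheap improvement. As scheduled, adverse effects of medication are not systematically captured at the end of the intervention. The first scheduled post-baseline question comes about 3 months later, and up to 10 of 50 patients would have none.

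The figure of 10 describes the gap under the present schedule. It should not be read as the benefit of the change, which among drop-outs lies anywhere from 0 to 10 patients. These numbers rest on the planned 20% drop-out being realised and on every drop-out missing t2. No aim, sample size or planned test is affected.

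**What to change.** Mark the self-reported adverse-effect item at t1 in Table 2, and amend the description of the t1 contact to match. Ask the same item, worded as at t0 and t2, in the existing telephone call, directly after the medication-change question. Report it descriptively at t1 and t2, with the number of patients answering at each time, split by whether medication was changed. State that, without a control arm, these figures do not support attribution to the intervention.

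The cost is a few more minutes per call, a slightly longer contact for the patient, and a minor amendment. No new instrument, staff or contact is needed. The change concerns data collection only and leaves clinical management as it is.
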